### Data integrity, management and monitoring

Hardcopy original data collection forms will be kept in a locked filing cabinet within a locked office. Electronic data will be stored in a purpose-built on-line database (www.adeptrs.com), with encryption and password protection. No identifying information will be stored in the online database. Electronic data for all sites will be accessible by the principal investigator and the trial coordinator. Site specific investigators will only have access to data relating to their individual site. The trial will be monitored by an independent Data Safety and Monitoring Committee (DSMB), chaired by a respiratory physician who is independent of the study team and trial sites. Any serious adverse events will be notified to the overseeing ethics committee (Alfred Health) and the relevant site governance committee, as well as to the DSMB.

## Discussion

Fibrotic ILD is a debilitating condition associated with significant dyspnoea, fatigue, and poor exercise tolerance. Considerable evidence exists that demonstrates PR is an effective intervention that can positively impact these aspects, yet a substantial proportion of participants are not achieving these benefits [12]. Optimising the exercise training approach for people with fILD ensures a greater proportion will achieve the health benefits associated with PR.

Currently the optimal exercise training strategy for people with fILD remains unknown. HIIT however offers promise. The basic premise of HIIT is that individuals are able to exercise at a higher intensity, albeit in short, repeated bouts, providing a greater training stimulus, particularly to the peripheral muscles, without increasing breathlessness or fatigue [23, 24, 28] potentially leading to superior physiological improvements. [28]. In COPD, despite marked heterogeneity in training volume, interval duration and intensity among protocols, HIIT was found to be equally effective to continuous training for improving functional capacity and HRQoL [27, 28, 69] whilst potentially inducing less symptoms of dyspnoea and leg discomfort [31, 32]. In ILD, the evidence for HIIT is limited to one feasibility study with a small sample size and variable intervals among participants [34]. This will be the first RCT to compare the clinical benefits of HIIT vs the commonly used method of MICT over the course of an 8-week PR program in people with fILD. A large sample size with recruitment across four sites, a diverse spectrum of meaningful outcomes that aim to capture endurance and functional exercise capacity, symptoms, muscles changes and daily activity, and a volume matched exercise protocol that is standardized across all the participating sites will ensure an impactful and high quality study.

This study will provide invaluable insight into the benefit of HIIT in fILD. The findings will demonstrate whether HIIT can produce equivalent or even superior improvements in exercise tolerance, symptoms and HRQoL to that of MICT in people with fILD. If HIIT proves successful, it will provide an important, readily available, exercise training strategy that can maximise the outcomes of PR for people with fILD.

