**Discussion:**

The standard exercise training strategies used in pulmonary rehabilitation may not provide an optimal exercise training stimulus for people with interstitial lung disease. This study will determine whether high intensity interval training can produce equivalent or even superior changes in exercise performance and symptoms. If high intensity interval training proves effective, it will provide an exercise training strategy that can readily be implemented into clinical practice for people with interstitial lung disease.

*Trial registration* ClinicalTrials.gov Registry (NCT03800914). Registered 11 January 2019, https://clinicaltrials.gov/ct2/show/NCT03800914

Australian New Zealand Clinical Trials Registry ACTRN12619000019101. Registered 9 January 2019, https://www.anzctr.org.au/Trial/Registration/TrialReview.aspx?id=376050&isReview=true

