In chronic obstructive pulmonary disease (COPD), meta-analyses concluded HIIT was equally effective as continuous training in producing beneficial physiological change and improvement in HRQoL [27–29]. Additionally, in some studies HIIT was found to be associated with less leg discomfort [30–32], less dyspnoea [30–32] and greater adherence [33] when compared to continuous training. In ILD, there is little evidence on the benefit of HIIT. One small feasibility study comparing the efficacy of HIIT vs continuous training in ILD of varying aetiology provided preliminary evidence (n = 36) that HIIT is as effective as continuous training [34], although the duration of intervals varied among HIIT participants. Interestingly in their subgroup analysis, HIIT was found to be more effective in patients with IPF, although the sample size was small (approximately n = 12) [34]. This preliminary evidence suggests HIIT may be a more achievable method for people with fILD to attain the recommended exercise training intensity that promotes health-enhancing benefit. A robust, high quality trial is necessary to establish whether HIIT is an effective exercise training strategy in fILD.

The primary aim of this study is to compare the clinical benefits of HIIT vs MICT in people with fILD. We hypothesise that HIIT will deliver clinically significant improvements in exercise endurance (primary outcome), symptoms and HRQoL, which are superior to those achieved with the MICT method typically used in PR.

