### Sample size

A total of 122 participants (61 per group) will be required to detect a clinically important difference between groups for the primary outcome measure of exercise endurance in the CWRT, with 80% power, and at the two-sided 5% level. This is based on the intermediate boundary (150 s) of the mean important difference range for the CWRT (SD = 292 s) [46, 68]. We will also be powered for the secondary outcome of HRQoL measured by the SGRQ-I based on data from our previous RCT of exercise training in ILD [11]. For HRQoL, a total of 114 participants are required to detect a mean difference of 6 points in SGRQ-I total score (SD = 11.3 points). In our previous trial, we had 5% attrition at completion of exercise training and 12% attrition at six months follow up [11]. Therefore, we will randomise a total of 130 participants, split evenly between groups.

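### The article promises a finding on equivalence, but its hypothesis and sample size serve superiority only, so a non-significant result could be misreported as equivalence

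*Protocol article*

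**What the plan says.** Two narrative statements promise an answer on equivalence. The Discussion part of the abstract says: "This study will determine whether high intensity interval training can produce equivalent or even superior changes in exercise performance and symptoms". The closing paragraph of the main Discussion widens this to quality of life: "The findings will demonstrate whether HIIT can produce equivalent or even superior improvements in exercise tolerance, symptoms and HRQoL to that of MICT".

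The operative sections say something narrower. The hypothesis at the end of the Background is that HIIT will bring improvements "which are superior to those achieved with the MICT method typically used in PR". Under Sample size, "A total of 122 participants (61 per group) will be required to detect a clinically important difference between groups", "with 80% power, and at the two-sided 5% level". The difference used there is 150 s with an SD of 292 s. The SGRQ-I calculation has the same form: "a total of 114 participants are required to detect a mean difference of 6 points in SGRQ-I total score (SD = 11.3 points"). Under Statistical analysis, continuous outcomes go into linear mixed models by intention to treat, with alpha 0.05.

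**The concern.** A superiority test that misses significance shows only that a difference was not detected. Concluding that two programmes are equivalent, or that one is at least as good as the other, needs a margin and a confidence interval that stays inside it. The article promises that conclusion, while its stated hypothesis and sizing aim at something else.

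This matters because a null result is realistic. The Background reports that meta-analyses in COPD found interval and continuous training equally effective. The abstract also follows its equivalence sentence directly with the prospect of use in clinical practice if HIIT proves effective. A reader, or the eventual results paper, could take a non-significant difference as the equivalence that was promised.

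**Working it through.** **Inputs.** From Sample size: difference 150 s, SD 292 s, 61 per group, 80% power, two-sided 5%; for SGRQ-I, 6 points, SD 11.3, total 114. The article gives no equivalence or non-inferiority margin, so the margins below are assumptions.

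**1. Reproduce the stated sample size.** The normal approximation gives n per group = 2 × [(1.960 + 0.842) × 292/150]² = 59.5, so 60 per group. The exact two-sample t calculation gives 61 per group, total 122, with power 80.4%. This matches the article. The same exact method gives 57 per group, total 114, for SGRQ-I, which also matches. Both figures are therefore standard superiority calculations.

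**2. Precision at that size.**
- SE = 292 × √(2/61) = 52.9 s.
- 95% half-width = 1.98 × 52.9 = about 105 s. An observed difference of zero gives an interval of about −105 to +105 s.
- For SGRQ-I, SE = 11.3 × √(2/61) = 2.05 and the half-width is about 4 points, against a target difference of 6.

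**3. How often a real deficit would go undetected.** P(non-significant) = Φ(1.96 − d/SE) − Φ(−1.96 − d/SE), where d is the true difference.
- HIIT truly 75 s worse: about 71%.
- HIIT truly 100 s worse: about 53%.

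**4. Power for the other conclusions.** The true difference is taken as zero, with 61 per group and margin M.
- Equivalence, two one-sided 5% tests: power = 2Φ(M/SE − 1.645) − 1.
- Non-inferiority, one-sided 2.5%: power = Φ(M/SE − 1.960).

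| Assumed margin | M/SE | Equivalence | Non-inferiority |
|---|---|---|---|
| 150 s | 2.837 | 77% | 81% |
| 100 s | 1.891 | 19% | 47% |
| 75 s | 1.419 | 0% | 29% |

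For 80% power at a 100 s margin, equivalence needs 2 × [292 × (1.645 + 1.282)/100]² = 147 per group, and non-inferiority needs 2 × [292 × (1.960 + 0.842)/100]² = 134 per group.

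**5. Sensitivity to baseline adjustment.** The article gives no baseline correlation and does not say whether 292 s is the SD of a single measurement or of change. If it is the former and the correlation is r, the SE is multiplied by √(1 − r²).
- r = 0.5: SE about 45.8 s, half-width about 91 s, equivalence power at 100 s about 41%.
- r = 0.7: SE about 37.8 s, half-width about 75 s, equivalence power at 100 s about 68%.

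If 292 s is already the SD of change, this gain does not follow.

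**The case against.** The strongest reply is that every operative section agrees with every other. Hypothesis, sample size and analysis all fit superiority, and the claim of equivalence for this trial sits only in two narrative sentences. Removing it would change no test, analysis population or number. That is correct, and it makes this a defect of stated purpose rather than of design.

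A second reply is that the article condenses a full protocol (version 5, cited under Design) and that an SAP may exist, so a margin could be written there. That also stands: the absence of a margin from the article is not an error in itself. What remains is that the hypothesis and sizing objective are given here, for superiority alone, and they do not match the promise.

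Third, the promised wording can be read as at least as good, which is non-inferiority and less demanding than two-sided equivalence. Baseline adjustment could also improve precision. Both points are fair, so the working shows both tests and the effect of adjustment. Neither supplies a margin.

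A reader might infer that the investigators will report a null result as equivalence. The article never says so; the wording only leaves that open. A reader might also infer that the trial is under-sized or the primary analysis wrong. The sample size reproduces exactly for its superiority purpose, so the documents do not support that either.

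**Conclusion.** The point holds as a conflict between what the article says the trial will show and what its hypothesis and sample size are built to show. It is a correction to two narrative sentences and a limit on what a null result may claim. It does not put the superiority comparison in doubt.

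On the stated inputs, without baseline adjustment, a null result would leave a deficit of about 105 s open. Power for equivalence or non-inferiority approaches 80% only with a margin near 150 s, which is the difference the sample size treats as clinically important. At 100 s it falls to about 19% or 47%. These power figures rest on assumed margins, a true difference of zero, SD 292 s and 61 per group analysed. A useful baseline correlation would raise them.

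**What to change.** Limit the claim to superiority wherever the trial's purpose is restated. Because the article is already published, the practical places are the SAP and the results report. Suggested text: *A non-significant difference will not be interpreted as equivalence. The 95% confidence interval for the between-group difference will be reported and discussed against the important difference used in the sample size (150 s for endurance time, 6 points for SGRQ-I).*

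If an at-least-as-good conclusion is wanted, specify and justify a margin for each outcome claimed, state the confidence-interval rule, and give the power available at the planned size. This should be done before any between-group results are seen. That is a clearer cut-off than unblinding, since participants are not blinded.

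The first option costs only wording, and its downside is a more modest claim if the result is null. The second also costs the work of justifying margins and, on the figures above, may show that the planned size is too small for a margin well below 150 s.

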### Trial status

Recruitment commenced in July 2019.

## Data Availability

The datasets used and/or analysed during the current study are available from the corresponding author on reasonable request.

## Abbreviations

6MWD: 6-Minute walk distance
6MWT: 6-Minute walk test
CWRT: Constant work rate test
COPD: Chronic obstructive pulmonary disease
CPET: Cardiopulmonary exercise test
CRQ: Chronic respiratory disease questionnaire
CTD-ILD: Connective tissue related ILD
DSMB: Data Safety and Monitoring Committee
FSS: Fatigue severity scale
fILD: Fibrotic interstitial lung disease
HADs: Hospital Anxiety and Depression Scale
HIIT: High intensity interval training
HP: Hypersensitivity pneumonitis
HRQoL: Health-related quality of life
IIP: Unclassifiable idiopathic interstitial pneumonia
ILD: Interstitial lung disease
IPF: Idiopathic pulmonary fibrosis
mMRC: Modified Medical Research Council
MICT: Moderate intensity continuous training
PR: Pulmonary rehabilitation
RA: Rheumatoid arthritis
RCT: Randomised controlled trial
SD: Standardised deviation
SpO_2_: Oxygen saturation
SGRQ-I: St George’s Respiratory Questionnaire idiopathic pulmonary fibrosis specific version
VO_2_: Oxygen consumption
Wpeak: Peak work rate
WHO: World Health Organisation
